### Data collection and management

During the recruitment period, researchers will record the baseline characteristics of participants in clinical record forms (CRFs). Data recorded on the original CRFs will be entered into Excel spreadsheets by two data managers independently. The data managers will cross-check the two data sets to ensure accuracy.

All documents related to clinical studies, such as CRFs, should be recorded and distinguished by the subject identification code, usually the subject’s initials, not the name. Records identifying the subject’s identity will be kept confidential, and the identity will also remain confidential on publication of the results of the clinical study.

If a subject prefers to discontinue participation, the researcher can stop the clinical study for the patient and arrange all the planned assessments at the final visit. In the case of a failed follow-up, researchers must demonstrate “reasonable effort” to contact the subject by documenting the actions taken (e.g., telephone contact date, registered mail, etc.) For patients opting to drop-out from the clinical trials, visits should be scheduled as soon as possible to conduct all the planned assessments at the final visit.

The datasets analyzed during the current study will be available from the corresponding author on reasonable request.

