**Fig. 2 Fig2:**
[figure not shown]
Standard Protocol Items: Recommendation for Interventional Trials (SPIRIT) schedule of enrollment, interventions, and assessments. GMFCS, Gross Motor Function Classification System; GMFM, Gross Motor Function Measure; K-BSID III, Korean Bayley Scales of Infant Development III; GAS, Goal Attainment Scale; PedsQL, Pediatric Quality of Life Inventory

The assessments will be performed three times in total: at baseline, 12 weeks (after 3 months), and 24 weeks (after 6 months). Two physical therapists with more than 5 years of experience in pediatric rehabilitation will evaluate the scores for each item and the recorded videos (the videos will be recorded by a physical therapist during assessment to evaluate the participants’ GMFM-88, GAS, and K-BSID III developmental status). In principle, the same person should conduct all three evaluations. Assessors will be blinded to the subject assignment, and an inter-rater reliability test will be conducted before each study. The proposed study protocol is schematically presented in Figs. 1 and 2.

Sample size calculations are based on a previous study [8]. We estimated a GMFM-88 score difference of 2.8 ± 3.2 (effect size, *d* = 0.8) which is considered to clinically indicate a change in motor function. A two-sided 5% significance level and 90% power were considered, and calculations indicated the requirement of approximately 28 participants in each group. Estimating a 30% dropout rate, each group will require 40 initial participants. Therefore, this study will be performed as a multicenter randomized controlled trial (RCT) by recruiting 80 subjects for a period of 2 years. Patients will be recruited from Pusan National University Hospital, Yangsan Pusan National University Hospital, Pusan Dongeui Hospital, and Bundang Cha Hospital.

In the event of a direct injury in relation to this study, appropriate medical action may be taken according to the decision of the clinical researcher. The level of compensation shall be an appropriate amount for the nature of the damage, its degree of consistency, and as would be generally decided by the courts in Korea and cover the entire treatment cost until the adverse event (AE) is cured. If rehabilitation therapy is required or an after-effect is noted, appropriate compensation will be provided after assessing the disorder.

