### Statistical analysis

Researchers will analyze for our main objective by comparing the outcomes (GMFM-88) of children receiving UR with IMR (group A) and those receiving UR without acupuncture and herbal medicine (group B) between baseline and 12 weeks. Within-group comparisons for changes in the duration of IMR and UR will be performed. We will use linear mixed models to test group differences in improvements over time for each outcome measure while adjusting for the serial correlation introduced by repeated measurements on the same participants. Group assignment, GMFCS level, time, and their interactions were included as fixed effects, with age as a fixed-effect covariate; patient and patient-by-time effects were included as random effects. A heterogeneous autoregressive covariance structure will be used for the random effects. Rates of change (slopes) from baseline to 12 weeks and from 12 to 24 weeks will be tested to evaluate treatment effects. Rates of change from baseline to 24 weeks will be compared with overall improvement across outcomes. Missing values will be imputed using the last-observation-carried-forward method.

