### Monitoring

If one of the following is encountered, it is possible to terminate the clinical trial early: (1) disease condition of the subject deteriorates and it is difficult to continue the research; (2) unexpected systemic diseases that were not detected before the study are diagnosed; (3) the subject or guardian requests the suspension of the examination; (4) self-treatment which may affect the judgment of the study results during the procedure period or the observation period; (5) the occurrence of serious AEs or the patient requires test termination due to AEs; (6) death of the subject; (7) violation of the plan for herbal medicines and medication; (8) subject cannot be tracked; (9) it is difficult for the research to proceed because of the medical staff’s judgment; and (10) treatment compliance is less than 50% (acupuncture or herbal medicine treatment).

Monitoring of clinical trials and auditing trial conduct will be carried out by the company designated by Pusan National University Hospital TKM Clinical Research Center via a regular once-monthly visit or telephonically. A Data Monitoring Committee was not considered as this was a low-risk intervention.

Monitoring personnel will monitor the progress of the clinical study and consult the researcher in case of a problem. Only the Principal Investigator can access the final dataset, and statisticians will be provided with a dataset blinded to group allocation. However, the TKM doctor cannot be blinded to group allocation, because acupuncture is possible only when the participant and the TKM doctor have contact.

Protocol amendments will be performed based on consensus by the Pusan National University Hospital TKM Clinical Research Center, and researchers will update the protocol in the Ministry of Food and Drug Safety Integrated Information System.

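### The protocol gives drop-outs only a prompt exit assessment and nowhere keeps the week-12 GMFM-88 for children who stop or are taken off early but could still attend

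*Protocol article*

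**What the plan says.** Data collection and management has two provisions for children who leave:

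- If a subject prefers to discontinue, "the researcher can stop the clinical study for the patient and arrange all the planned assessments at the final visit".
- For those who opt to drop out, "visits should be scheduled as soon as possible to conduct all the planned assessments at the final visit".

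Monitoring lists ten grounds for early termination, most of them worded for an individual child. They include "disease condition of the subject deteriorates and it is difficult to continue the research", self-treatment, serious adverse events, violation of the herbal medicine and medication plan, and "treatment compliance is less than 50% (acupuncture or herbal medicine treatment".

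Statistical analysis sets the main objective as the GMFM-88 comparison of children on UR with IMR (group A) and "those receiving UR without acupuncture and herbal medicine (group B) between baseline and 12 weeks". Table 2 schedules GMFM-88 only at baseline, 12 weeks and 24 weeks. Missing values are to be filled by last observation carried forward (LOCF).

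The sample size paragraph in Study design plans for loss: "Estimating a 30% dropout rate, each group will require 40 initial participants".

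**The concern.** The article draws no line between a child who stops treatment and a child whose guardian refuses further assessment. The only assessment it describes for a child who leaves is the exit assessment, which for drop-outs is brought forward to the time of leaving. A child who left in week 3 and took that visit would have a GMFM-88 score from about week 3. Nothing in the text then calls the child back at week 12.

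Two features make this more than a loss of numbers:

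- **Leaving may be related to the outcome.** Deterioration is one of the listed grounds.
- **Leaving may be related to the arm.** Group B receives neither acupuncture nor herbs in weeks 1–12, so the compliance ground and the herbal part of the plan-violation ground can remove only group A children in that window.

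LOCF then gives the gap a value, either the early exit score or, if there was no exit visit, the baseline score. At stake is whether the 12-week contrast still compares the groups as randomised.

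**Working it through.** **1. The plan's own figures.** Inputs from Study design: difference 2.8, SD 3.2, two-sided 5%, power 90%, dropout 30%.

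- n per group = 2 × (1.960 + 1.282)² / (2.8/3.2)² = 2 × 10.51 / 0.766 = 27.4, so 28.
- 28 / (1 − 0.30) = 40 per group.

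Both reproduce. Planned dropout is therefore 12 of 40 per group, 24 of 80 in all.

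**2. How many could be affected.** The 30% has no time point, and the study lasts 24 weeks. A child who leaves in weeks 13–24 already has a week-12 score, so 12 per group is a ceiling. If exits were spread evenly over 24 weeks (an assumption), 15%, or 6 per group, would leave before week 12. How many of those could still attend is not given.

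**3. What the rule does, compared with what the fix would deliver.** Assumptions, none from the document:

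- Shares dA and dB leave before week 12, with exits even over weeks 0–12.
- Gain is linear, so an exit score holds on average half of the 12-week gain.
- Both groups have a natural gain g on UR.
- Group A leavers who are measured at week 12 keep half of the 2.8, and all leavers attend.

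Then:

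- Exit score used as week 12: D_rule = (g + 2.8)(1 − dA/2) − g(1 − dB/2)
- Week-12 score collected: D_fix = 2.8(1 − dA/2)
- Difference due to the rule: D_rule − D_fix = −g(dA − dB)/2

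| dA / dB | g | D_fix | D_rule | Due to the rule |
|---|---|---|---|---|
| 30% / 30% | any | 2.38 | 2.38 | 0 |
| 40% / 20% | 2 | 2.24 | 2.04 | −0.20 (−9%) |
| 40% / 20% | 4 | 2.24 | 1.84 | −0.40 (−18%) |
| 20% / 40% | 2 | 2.52 | 2.72 | +0.20 (+8%) |
| 20% / 40% | 4 | 2.52 | 2.92 | +0.40 (+16%) |
| 20% / 10% | 2 to 4 | 2.52 | 2.42 to 2.32 | −0.10 to −0.20 (−4% to −8%) |

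Under these assumptions, equal dropout produces no bias from the rule. Unequal dropout does, and the sign follows the arm that loses more children. The formula leaves out selection, such as children ended because they worsened, whose size cannot be worked out from the document.

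**4. Power.** By t-test at 2.8/3.2, 28 per group gives 89.5%. If half of 12 leavers attended week 12 and kept the full effect, 34 per group would give 94.5%. If the six extra group A children kept half the effect, the mean effect would be 2.8 × (28 + 3)/34 = 2.55 and power about 90%. The gain then nearly vanishes.

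**The case against.** The strongest reply is about scope. The two provisions in Data collection and management are triggered by families who are leaving the trial, not by stopping acupuncture or herbs. A prompt exit assessment is ordinary practice for them. The wording on discontinuation is permissive, and only the drop-out sentence calls for haste. Monitoring says that termination is possible. It does not say that outcome assessment ends, and a child who has deteriorated badly may be unable to attend. The article also condenses a fuller protocol.

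Much of this stands. A reader might infer that every child who stops is barred from the week-12 visit. The text does not say so. It also does not say the opposite, and the one arrangement it does fix is an early visit. Together with grounds for ending participation that need not prevent attendance, and with LOCF, that is a stated rule with a consequence and not only an omitted detail.

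Three stronger readings are tempting, and the documents do not support them:

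- **That 30% of week-12 scores are lost.** The rate has no time point and is only an upper bound.
- **That the rule costs 15% of the effect, or 27% to 34% with unequal dropout.** Those figures compare 2.38, or 2.04 to 1.84, with a full 2.8. The fix would not restore 2.8, because children who stop IMR early may keep only part of its effect. The 40%/20% split and the gain of 2 to 4 points also have no source in the article.
- **That no analysis could use an exit score.** The model tests rates of change with patient-by-time random effects, and the article does not say that time is categorical, so a dated exit score could enter it. It still would not be a week-12 measurement. Whether LOCF is a good choice is a separate matter and is not counted here.

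**Conclusion.** The point holds in a limited form. As written, the plan provides only an exit assessment for children who leave, allows participation to be ended on grounds compatible with attending week 12, and protects the primary week-12 GMFM-88 for none of these children. Some of those grounds can operate only in group A within the primary window, so losses may differ by arm.

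The harm is potential bias in the randomised 12-week comparison. It is not a shortfall in power, because 28 was already raised to 40 for this loss. The size cannot be fixed from the document. At most 12 per group are affected under the planned dropout, and fewer if some leave after week 12. In the illustration, the part due to the rule runs from zero with equal dropout to 0.4 points in either direction with a 20-point imbalance and a natural gain of 4. That range rests wholly on assumed exit timing, linear gain, half effect retained, full attendance and use of the exit score as the week-12 value. The change is worth making before recruitment opens, because an outcome not measured at week 12 cannot be recovered later.

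**What to change.** In Data collection and management and in Monitoring:

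1. Separate stopping treatment, or being ended on one of the listed grounds, from refusing further assessment.
2. Ask every such child whose guardian still agrees to attend the scheduled week-12 and week-24 assessments with the blinded assessors, and analyse those scores in the group assigned.
3. Keep the exit visit for safety and as a fallback when the guardian refuses further assessment. Record its actual date and do not relabel it as week 12.

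The grounds for stopping treatment stay as they are. The cost is protocol wording and keeping appointments that are already in the schedule, with no new assessor or procedure. Some guardians will decline, and the comparison will include children no longer on IMR, which fits a trial that calls itself pragmatic.

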### Monitoring

If one of the following is encountered, it is possible to terminate the clinical trial early: (1) disease condition of the subject deteriorates and it is difficult to continue the research; (2) unexpected systemic diseases that were not detected before the study are diagnosed; (3) the subject or guardian requests the suspension of the examination; (4) self-treatment which may affect the judgment of the study results during the procedure period or the observation period; (5) the occurrence of serious AEs or the patient requires test termination due to AEs; (6) death of the subject; (7) violation of the plan for herbal medicines and medication; (8) subject cannot be tracked; (9) it is difficult for the research to proceed because of the medical staff’s judgment; and (10) treatment compliance is less than 50% (acupuncture or herbal medicine treatment).

Monitoring of clinical trials and auditing trial conduct will be carried out by the company designated by Pusan National University Hospital TKM Clinical Research Center via a regular once-monthly visit or telephonically. A Data Monitoring Committee was not considered as this was a low-risk intervention.

Monitoring personnel will monitor the progress of the clinical study and consult the researcher in case of a problem. Only the Principal Investigator can access the final dataset, and statisticians will be provided with a dataset blinded to group allocation. However, the TKM doctor cannot be blinded to group allocation, because acupuncture is possible only when the participant and the TKM doctor have contact.

Protocol amendments will be performed based on consensus by the Pusan National University Hospital TKM Clinical Research Center, and researchers will update the protocol in the Ministry of Food and Drug Safety Integrated Information System.

## Discussion

The aim of this trial is to investigate the efficacy and safety of IMR for children with CP in Korea. The results will help to demonstrate if IMR is an effective therapeutic approach for CP.

In a systematic review of the effects of acupuncture and herbal medicines in Chinese children with CP, six out of 35 RCTs reported AEs; however, these were not associated with acupuncture and herbal medicine treatment [6]. Despite the safety of acupuncture and herbal medicines, no large-scale RCTs have been conducted in Korea. This lack of evidence necessitates an additional RCT to evaluate the clinical efficacy of integrative medicine in patients with CP.

The acupuncture program includes body acupuncture and press needle acupuncture. The acupoints for body acupuncture include five head points (GV20, EX-HN1) and 12 limb points (bilateral LI4, LI11, LU9, ST36, LR3, and BL60). In cases of spastic CP, additional press needles will be used on the wrists and ankle joints (LI5, TE4, BL60, and KI4). A systematic review of literature in Korea and China has identified these acupoints to be effective for paralysis and cognitive impairment [10, 27, 28].

The herbal medicine to be used in this study is a combination of Yukgunza-tang extracts and Yukmijihwang-tang extracts. Yukmijihwang-tang extract has been reported to improve cognitive and motor function in experimental and clinical studies in children with CP [5, 12–15]. In contrast, Yukgunza-tang extracts have been used to improve the gastrointestinal function of children with CP, promote the absorption of Yukmijihwang-tang extract (K-13), and prevent digestive disorders as a result of Yukmijihwang-tang extract (K-13) administration [16, 17].

The primary outcome is the GMFM-88 score which assesses large motor function in CP. The secondary outcomes are the GAS, K-BSID III, and PedsQL™ scores and AEs. A limitation of this study is that UR is not fully controlled because this study is a pragmatic RCT. This study could potentially confirm whether integrative medicine is an effective rehabilitation therapy for CP. Our study may show that IMR is effective and safe for treating motor dysfunction, language disorder, and social-emotional disorders in children with CP.

### Trial status

Protocol version number and date: 20170079446_Ver 1.2 and 21 June 2017.

Date recruitment will begin: January 2021.

Approximate date when recruitment will be completed: December 2022.

## Data Availability

Only the principal investigator of this study can access the final dataset and disclose contractual agreements, which limits the access for other investigators. The data generated here will be deposited at the Clinical Research Information Service (https://cris.nih.go.kr/) and other researchers can access those data upon request.

## Abbreviations

AE: Adverse event
CP: Cerebral palsy
CRFs: Clinical record forms
GAS: Goal Attainment Scale
GMFCS: Gross Motor Function Classification System
GMFM-88: Gross Motor Function Measure-88
HRQOL: Health-related quality of life
IMR: Integrative medicine rehabilitation
K-BSID III: Korean Bayley Scales of Infant Development III
PedsQL: Pediatric Quality of Life Inventory
RCT: Randomized controlled trial
TKM: Traditional Korean medicine
UR: Usual rehabilitation
